### Implementation {16c}

The allocation sequence is computer-generated. The central research coordinator enrolls eligible patients into the study and assigns participants to interventions. Patients who are randomly allocated to the intervention arm are offered the intervention by the research coordinator and asked to provide additional informed consent for participation in the intervention arm of the trial.

## Assignment of interventions: blinding

### Who will be blinded {17a}

Blinding is not applicable to this TwiCs study. As part of the TwiCs design, however, patients randomized to the control arm and their treating clinicians will not be further notified.

### Procedure for unblinding if needed {17b}

Unblinding is not applicable to this TwiCs study as blinding is not applied.

### Data collection and management

#### Plans for assessment and collection of outcomes {18a}

Baseline characteristics of all trial participants are standardly collected as part of the PACAP and PACOPS projects. Also, quality of life is already assessed using PROMs at standardized time points in all participants. Data management is carried out in accordance with UMC Utrecht Data management policy, as described in the Data Management Plan. Data is collected using a predefined, electronic case record form in Castor EDC. Local clinicians in the participating centers are responsible for data collection. They can, however, transfer this responsibility to the study team. The study team will appoint appropriate personnel for data collection.

### Plans to promote participant retention and complete follow-up {18b}

The central research coordinator plays an essential role in participant retention and complete follow-up. All follow-up appointments will be scheduled by the research coordinator in consultation with the treating clinician and patient. Participants of the study are therefore followed closely by the research coordinator. In case test results are available, the research coordinator ensures that the results are discussed with the patient and in a multidisciplinary team meeting, if desired.

### Data management {19}

Data management will be carried out in accordance with the UMC Utrecht Data management policy, as described in the Data Management Plan. Data will be collected using a predefined, electronic case record form in Castor EDC. Subjects will be entered into the patient database at each of the participating centers. Local personnel per participating center is responsible for data collection. They can, however, delegate this to the study steering committee who will appoint an appropriate data management team per site. All data will be collected using a predefined, electronic case record from. Data will be handled confidentially and coded. The data will be kept for a minimum of 15 years.

### Confidentiality {27}

The handling of personal data will comply with the Regulation (EU) 2016/679 of the European Parliament and of the Council of 27 April 2016 on the protection of natural persons with regard to the processing of personal data and on the free movement of such data (General Data Protection Regulation). A subject identification code list will be used to link the data to the subject. These codes will not be based on the patient initials and birth date. The local investigators will safeguard the key to this code.

### Plans for collection, laboratory evaluation, and storage of biological specimens for genetic or molecular analysis in this trial/future use {33}

Not applicable.

### Statistical methods

#### Statistical methods for primary and secondary outcomes {20a}

The latest version of R Studio will be used for statistical analysis.

Baseline characteristics will be reported using standard descriptive statistics. Success of randomization will be evaluated by eye-balling whether the distribution of baseline characteristics between the intervention and control group is even. Primary analysis will be performed according to the intention-to-treat principle. As such, patients randomized to the intervention arm of the trial who refuse recurrence-focused surveillance following the TwiCs design will be analyzed as part of the intervention group. The main study parameter is overall survival, measured as the time from the date of PDAC resection to the date of death. Patients are censored at the time of last known follow-up visit documented if no event occurred. Overall survival rates will be reported as median with 95% CI and will be calculated by the Kaplan–Meier survival curve method. Log-rank test will be used to compare survival between the intervention and control group. One- and 2-year survival probabilities will be calculated. Univariate Cox-proportional hazard analysis will be used to assess the crude effect of a recurrence-focused surveillance strategy on survival. In addition, adjusted effect estimates will be calculated using a multivariable Cox-proportional hazard model, including potential confounders for symptomatic PDAC recurrence. To address potential confounders for which the multivariable analysis needs to be adjusted, a Directed Acyclic Graph was designed on https://www.dagitty.net (Fig. 3). It is hypothesized that a recurrence-focused postoperative surveillance strategy leads to the detection of PDAC recurrence in an asymptomatic stage, which increases the probability to undergo treatment for recurrence, possibly improving survival. The association between postoperative surveillance strategy and overall survival is therefore fully mediated through presence of symptoms at the time of recurrence diagnosis and subsequent administration of recurrence treatment. Given that the median overall survival after resection of PDAC is 21 months and 1- and 2-year survival rates are 75% and < 50%, respectively, we expect that during our follow-up period at least 50% of included patients (*n* = 153) will experience an event. The number of variables included in the multivariable analysis is based on the rule of thumb of ~ 10 events per variable, where a categorical variable counts for the number of categories. Consequently, multivariable analysis is adjusted for 15 baseline covariates that are considered to be the most important, i.e., age (continuous), sex (male/female), and predictors that reflect an (un)favorable tumor biology or treatment course, including performance status (continuous), preoperative CA 19–9 value (continuous), tumor location (head/distal), resection margin status (R0/R1), tumor size (continuous), number of positive lymph nodes (continuous) and tumor differentiation (poor/well-moderate), and administration of adjuvant therapy (yes/no). Given that recurrence treatment is considered a mediator, and not a confounder, no adjustment for recurrence treatment is required. Because administration of neoadjuvant therapy is known to affect preoperative CA 19–9 values, resection margin status, tumor size, and number of positive lymph nodes, neoadjuvant treatment will not be adjusted for. Postoperative complications are deemed to affect the receipt of adjuvant therapy and will thus not be included in multivariable analysis. Results will be presented as hazard ratio’s (HR) with corresponding 95% confidence intervals (CI). A two-tailed *P-*value < 0.05 will be considered statistically significant.

Data on the incidence of PDAC recurrence, compliance to a recurrence-focused surveillance strategy, clinical, and radiological patterns of recurrence, eligibility for treatment of recurrence, administration of recurrence treatment, as well as type of treatment, reasons to refrain from recurrence treatment, and patient tolerance to recurrence treatment (i.e., completion of treatment as planned) will be analyzed and reported using descriptive statistics. Chi-square or Fisher’s exact test are used to compare categorical variables as appropriate. Parametric continuous variables are presented as mean ± standard deviation (SD) and are compared using the Student’s *t*-test. Non-parametric continuous variables are presented as median with interquartile range (IQR) and are compared using the Mann–Whitney *U* test. Patient-reported outcomes at each time point during follow-up will be compared to baseline scores using a generalized linear mixed model approach to assess a difference in patients’ quality of life and worry of cancer recurrence between the trial arms. Scores will be presented as mean (± SD), changes from baseline as mean differences (MD) and estimates will be calculated to represent a difference in MD between groups with corresponding 95% confidence intervals (CI). Minimally important differences (MIDs) for the EORTC QLQ-C30 will be interpreted based on Musoro et al. for available quality of life domains [34]. If not specified, a ≥ 10-point change is considered meaningful. Disease-free survival and post-recurrence survival will be assessed using Kaplan–Meier survival curves and reported as median with 95% CI. The log-rank test will be used to compare groups. Cox proportional hazards model will be used when appropriate. Stratified analyses will be performed regarding pattern of disease recurrence and type of additional treatment. Various baseline parameters (e.g., sex, age, body mass index (BMI), Charlson Comorbidity Index (CCI), ECOG score, postoperative complications, (neo)adjuvant therapy, resectability status, preoperative CA 19–9 values, tumor location, resection margin status, vascular resection, tumor (T) stage, lymph node (N) stage, tumor differentiation, perineural growth) will be collected. The yield of CT surveillance and role of serum tumor marker testing is assessed by calculating diagnostic accuracy values, i.e., sensitivity, specificity, false-positive and false-negative values. Cost-effectiveness is calculated using a Markov model.

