### Interventions

#### Explanation for the choice of comparators {6b}

Participants in the control arm of the RADAR-PANC trial will receive non-standardized clinical follow-up, according to local practice in the participating hospital. As the most recent version of the national Dutch guideline for PDAC care currently does not recommend a recurrence-focused follow-up frequency, methodology, or focus, follow-up after PDAC resection is based on shared decision-making, at the discretion of the treating clinician and the patients’ wish [15].

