### Intervention description {11a}

The intervention exists of a recurrence-focused follow-up approach with routine imaging and serial serum tumor marker testing. The follow-up scheme of the RADAR-PANC trial is based on current surveillance guidelines after resection for PDAC as recommended by the National Comprehensive Cancer Network (NCCN) [11]. This intense follow-up scheme was chosen to increase the chance of early diagnosis of disease recurrence. For the first 2 years after surgery, clinical evaluation, serum carbohydrate antigen 19–9 (CA 19–9) testing, and contrast-enhanced CT imaging of chest and abdomen is performed every 3 months.

Follow-up of patients and related procedures (i.e., blood draws, CT scans) in this study can be performed at the participating hospital, referring hospital, or central coordinating hospital. Study-related follow-up is performed at 3, 6, 9, 12, 15, 18, 21, and 24 months after surgery. For the first follow-up evaluation, patients need to be randomized within the first 3 to 4 months post-surgery. Follow-up appointments are made by the trial coordinator in consultation with the treating clinician. If possible, outpatient clinic visits are combined with CT scan appointments; blood samples are obtained simultaneously.

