#### Recurrence diagnosis

If disease recurrence (local and/or distant) is suspected on the basis of a follow-up CT scan, with or without elevated tumor markers, pathological confirmation is strongly advised. If the results remain inconclusive or pathology cannot be obtained, additional imaging (magnetic resonance imaging (MRI) and/or positron emission tomography CT (PET-CT)) may be considered. Consensus on the presence of a recurrence should be obtained in a multidisciplinary meeting (e.g., based on imaging, elevated CA 19–9, and clinical evaluation).

If disease recurrence is diagnosed, best supportive care (BSC) or systemic and/or local therapy is offered at the discretion of the treating clinician in both trial arms, which is the current standard practice, and trial-related follow-up will end. It is encouraged to offer treatment to all patients in whom there are no contraindications based on clinical condition (performance status), comorbidity, or specific exclusion criteria for systemic and/or local therapy. Patients can be offered to participate in intervention trials on management of pancreatic cancer recurrence. In the Netherlands, within the DPCG, two intervention studies for the treatment of PDAC recurrence have been simultaneously initiated: the ARCADE trial (NCT04881487), investigating the efficacy of stereotactic body radiation therapy on survival after recurrence and quality of life in patients with isolated local PDAC recurrence, and the TIMEPAN trial (NCT04897854) studying the optimal timing of start of systemic treatment for asymptomatic metastasized PDAC.

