### Provisions for post-trial care {30}

Individual patients will remain enrolled in the RADAR-PANC trial for a maximum of 2 years or until patient withdrawal. Follow-up of patients that have completed the 2-year follow-up will be continued for survival information until death. Patients who are withdrawn from the study will be followed-up by a medical specialist or general practitioner for survival information until death. After the study period has ended for an individual patient, continuation of either recurrence-focused or non-standardized follow-up and diagnostic testing is based on shared decision-making between patients and their treating physicians.

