### Outcomes {12}

The primary outcome is overall survival, defined as the time from the date of PDAC resection until the date of either death from any cause or last follow-up.

Secondary outcomes are the following:Patient-reported quality of life and worry of cancer recurrence, as measured by PROMs questionnaires within the PACAP-PROMs and PACOPS project: general EORTC QLQ-C30 and EQ5D-5L, pancreas-specific EORTC QLQ-PAN26, HADS, and WOPS.Compliance to recurrence-focused surveillance, measured as the percentage of patients that either accepts or refuses participation in the intervention-arm, i.e., is willing to undergo recurrence-focused follow-up.Disease-free survival, defined as the interval between the date of PDAC resection and the date of first radiological signs of recurrence, or last follow-up if recurrence is not observed. Preferably, recurrence is proven by a biopsy showing pathological confirmation of recurrent PDAC. However, recurrence can be clinically confirmed with growth of a suspicious lesion on consecutive CT scans and elevation of CA 19–9 (> 37 U/ml) and/or activity on PET-CT following consensus in a multidisciplinary meeting.Clinical and radiological patterns of disease recurrence:◦ Asymptomatic recurrence is defined as PDAC recurrence detected by CT imaging during follow-up, in the absence of suspected symptoms. If PDAC recurrence is discovered due to a significant patient-initiated complaint that is new or has been increased in severity or frequency, disease recurrence is defined as symptomatic.◦ Localization of recurrence is categorized using five categories: (1) isolated locoregional recurrence: recurrence in the pancreatic remnant, locoregional lymph nodes, or surgical bed, such as soft tissue along the celiac or superior mesenteric artery, aorta, or around the pancreatojejunostomy site; (2) isolated distant recurrence: recurrence restricted to a single organ or site; (3) local + distant recurrence: simultaneous occurrence of both isolated locoregional recurrence and isolated distant recurrence; (4) multiple recurrence: recurrence at multiple distant sites; and (5) peritoneal carcinomatosis.The yield of CT surveillance and role of serum tumor marker testing in detecting PDAC recurrence, by calculating diagnostic accuracy values, i.e., sensitivity, specificity, positive predictive values, and negative predictive values.Eligibility for additional (experimental) treatment at time of recurrence diagnosis, based on the Eastern Cooperative Oncology Group (ECOG) or Karnofsky performance state, or inclusion criteria for study-related treatment of recurrence.Reasons to refrain from treatment for recurrence (i.e., non-eligibility, deteriorated condition, patient’s wish, doctors’ advice, progression during treatment, etc.).Patients’ tolerance to treatment for recurrence, measured by the reasons to stop treatment for recurrence (i.e., per protocol, deteriorated condition, patient’s wish, doctors’ advice, progression during treatment etc.).Morbidity associated with recurrence-focused treatment.Overall costs of recurrence-focused surveillance vs. costs as incurred with current non-standardized follow-up. Cost-effectiveness is examined through the EQ5D questionnaire and calculated using a Markov model.

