### Recruitment {15}

To achieve adequate patient enrolment and reach the target sample size, all centers are encouraged to participate in the current trial. To ensure enrolment of all eligible patients, the study coordinator(s) are in close contact with the local investigators at the participating centers to obtain weekly updates about patients who underwent macroscopically radical PDAC resection. Eligible patients will be contacted by the study coordinators in consultation with the treating clinicians. If an eligible patient is not yet approached for participation in the PACAP or PACOPS project, informed consent for PACAP or PACOPS, including TwiCs and PROMs, will be discussed by the study coordinator(s).

In 2018, 2348 patients were diagnosed with pancreatic cancer in the Netherlands. About 20% (*n* = 470) of these patients underwent macroscopically radical (R0-R1) resection of the tumor. In the Netherlands, all pancreatic resections are performed in centers affiliated with the DPCG, which will all participate in the current study. Based on the current successful enrolment progress, we anticipate that 75% (*n* = 353) of all patients will be registered yearly in the PACAP cohort and that 80% (*n* = 282) of these patients will provide informed consent for the TwiCs design. About 150 patients each year are expected to be included in other studies with a study-specific follow-up, which is an exclusion criterium for the RADAR-PANC trial. This leaves 282 – 150 = 132 patients eligible for randomization in the current study each year. Fifty percent (*n* = 66) of patients will be randomized to a standardized surveillance strategy. We expect that 80% (*n* = 53) of these patients are willing to participate in the intervention arm of the study, with a participation rate of 100% (*n* = 66) in the control arm as a consequence of the TwiCs design. The expected time needed for inclusion of a total of 306 patients (153 patients in each arm) is therefore 28 months. The final analysis will be performed 30 months after the last patient is enrolled.

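### Censoring survivors at their last documented visit, while survival is traced until death, makes censoring depend on outcome and can distort the primary overall survival comparison

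*Protocol article*

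**What the plan says.** All references are to the protocol article.

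- **Statistical methods {20a}**, on the primary endpoint: "Patients are censored at the time of last known follow-up visit documented if no event occurred". The stated date is that of a visit.
- **Outcomes {12}** runs overall survival from resection "until the date of either death from any cause or last follow-up". No visit is mentioned.
- **Provisions for post-trial care {30}**: "Follow-up of patients that have completed the 2-year follow-up will be continued for survival information until death". The same holds after withdrawal: "Patients who are withdrawn from the study will be followed-up by a medical specialist or general practitioner for survival information until death". The section leaves clinical follow-up after the study period to shared decision-making in both arms.
- **Intervention description {11a}**: "Study-related follow-up is performed at 3, 6, 9, 12, 15, 18, 21, and 24 months after surgery".
- Section **{6b}**, on how controls are seen: "Participants in the control arm of the RADAR-PANC trial will receive non-standardized clinical follow-up, according to local practice in the participating hospital".
- **Recurrence diagnosis**: once recurrence is diagnosed, "trial-related follow-up will end".
- **Recruitment {15}**: accrual is expected to take 28 months, and "The final analysis will be performed 30 months after the last patient is enrolled".

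**The concern.** Put {20a} beside {30}. A patient who dies at month 40 is found by the survival tracing and enters as an event at month 40. A patient known to be alive at month 40 whose last documented visit was at month 24 leaves the risk set at month 24. Whether the time from month 24 to month 40 counts therefore depends on whether the patient died. That is outcome-dependent censoring, which the Kaplan–Meier, log-rank and Cox methods named in {20a} do not allow for.

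Two consequences follow. First, if the gap between last documented visit and cut-off differs by arm, the arm with the longer gap looks worse than it is. The documents give some reason to expect a difference: coordinator-arranged three-monthly visits to month 24 in one arm, local practice in the other. Second, even with identical gaps, discarding survivors' time lowers late survival estimates and can shrink a real effect. Both concern the primary endpoint.

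**Working it through.** **1. Inputs from the article.** Sample size {14}: 306 patients, control median 19.7 months, intervention median 29.4 months, 80% acceptance. Recruitment {15}: 28 months of accrual, then 30 months.

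**2. The plan's own figures.** Control hazard = ln 2 / 19.7 = 0.0352 per month, matching the stated 3.5%. Ratio of medians = 29.4 / 19.7 = 1.49, as stated. The design hazard ratio is 1 / 1.49 = 0.67.

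**3. Reference case: survivors censored at cut-off.** With uniform accrual over 28 months, follow-up runs from 30 to 58 months. The probability of death by cut-off is 1 − (e^(−30λ) − e^(−58λ)) / (28λ).
- Control, λ = 0.0352: 0.779.
- Intervention, λ = 0.0352 / 1.49 = 0.0236: 0.640.
- Events = 153 × (0.779 + 0.640) ≈ 217.
- Power = Φ(ln 1.49 × √217 / 2 − 1.96) = Φ(0.98) ≈ 0.84.

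Simulation gives the same 84%. This is not the plan's 80%: it includes the accrual period and leaves out the 1% monthly drop-out. It serves only as the comparator below.

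**4. Why month 24 matters.** The shortest follow-up at analysis is 30 months, so every survivor is past the visit schedule. Suppose last visits fall at month 24 in both arms. After month 24 the risk set then holds only patients who go on to die before cut-off, so the Kaplan–Meier curve must fall to zero.
- Control survival at month 24 = e^(−0.0352 × 24) = 0.43. The control median has already passed and is not affected.
- Intervention survival at month 24 = e^(−0.0236 × 24) = 0.57. The intervention median lies in the distorted region and is pulled down.

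**5. Simulation.** 306 patients, 1:1, exponential survival, all deaths to cut-off counted, survivors censored at the last visit, 80% acceptance with refusers following the control pattern. The runs used about 2,000 trials per scenario, so the simulation error is about half a percentage point at 5% and about one point at 27%. **All visit patterns are assumptions.**

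| Last documented visit of survivors | Null HR | Two-sided error |
|---|---|---|
| Both arms at cut-off | 1.00 | 5.5% |
| Similar later visits (6- or 12-month gaps in both arms after month 24) | 1.00 | 4.5% to 5.5% |
| Accepters 6-month gaps after month 24, others 12-month gaps | 0.97 | 5.8% |
| Accepters month 24, others month 18 | 0.94 | 8.3% |
| Accepters month 24, others month 12 | 0.88 | 17.4% |
| Accepters month 24, others within 12 months of cut-off | about 1.16 | about 20% |
| Accepters month 24, others within 6 months of cut-off | about 1.20 | about 27% |
| Both arms at month 24 | 1.00 | 5.0% |

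Under a true hazard ratio of 0.67:
- Both arms at cut-off: hazard ratio 0.67, intervention median 29.5 months, power 84%.
- Both arms at month 24: hazard ratio 0.73, intervention median 26.0 months, power 62% to 63%.
- Accepters at month 24, others within 6 months of cut-off: hazard ratio 0.86, power about 20%.

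**The case against.** The strongest reply is that the harm is conditional. Bias between arms needs three things together: deaths after the last visit are counted, contacts that show a patient alive are not used as the censoring date, and the gap to cut-off differs by arm. The tracing in {30} is itself called follow-up and yields dates alive as well as deaths. The endpoint in {12} ends at last follow-up. On that reading a survival contact could supply the censoring date, and the problem goes away.

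The documented visit difference also covers months 3 to 24, whereas after month 24 both arms have the same arrangement. Ending trial follow-up at recurrence does not mean that clinical visits end, and both arms are followed through the cohorts. Cut-off dates and vital-status sources are often left to an analysis plan that is not shown here.

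Most of this stands, and it rules out stronger readings that a reader might infer:

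- **That the rule does bias the result.** The documents do not fix the conditions. They support only that it can.
- **That deaths are counted without limit.** They count only up to the final analysis.
- **That the null hazard ratio is 1.24 to 1.29 with 37% to 48% error.** This requires every intervention patient to accept and none to have a documented visit after month 24. The protocol expects 20% refusal. If, in addition, half of the accepters have later visits like those of controls, the figures fall to about 1.07 to 1.08 and 8%.

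Two things remain. The rule in {20a} is stated, not left out, and it names a visit, so the article gives two different end dates for its primary endpoint. And a difference between arms is not needed for harm: last visits at month 24 in both arms already cost about 21 points of power (84% − 63%).

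**Conclusion.** The concern holds as a conflict between {20a}, {12} and {30} on the primary endpoint. Applied literally, the rule in {20a} makes censoring depend on outcome and can move the comparison in either direction. The effect ranges from none, with similar later visits in both arms, to a null hazard ratio of 0.88 one way or about 1.20 the other under the assumed patterns. With visits ending at month 24 in both arms it gives no false positives but weakens a true effect.

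The sizes rest on exponential survival, no drop-out and assumed visit patterns after month 24, which the article does not give. The existence of the conflict rests on none of these. It should be settled before the final analysis.

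**What to change.** Replace the censoring sentence in {20a}, and align {12} and {30} with it, along these lines:

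*Vital status is ascertained in both arms in the same way at one data cut-off date. Patients confirmed alive at or after the cut-off are censored at the cut-off. All others not known to have died are censored at the date last confirmed alive from any source, regardless of clinic visits. Deaths after the cut-off are not counted.*

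Patients of unknown status should not be censored at the cut-off, because that would treat them as alive. In the simulation, cut-off censoring with complete vital status gives a hazard ratio of 1.00 under the null and 0.67 under the design effect.

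The cost is a short text change and one vital-status check at cut-off, which the survival follow-up already planned in {30} supports.

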**Fig. 2 Fig2:**
[figure not shown]
Kaplan–Meier curve comparing overall survival between patients with routine follow-up imaging and symptomatic follow-up in the Netherlands between 2014–2019 (unpublished data)

As we expect 80% of patients to accept the experimental intervention offered in the intervention arm of the study, an estimated refusal rate of 20% needs to be taken into account. This leads to a decrease of the overall survival to 29.4 months (80% × 32.0 months + 20% × 19.0 months) for patients in the intervention arm. Moreover, despite that current non-standardized follow-up in daily clinical practice mainly results in a symptomatic follow-up approach without routine imaging, data from our recurrence database showed that 85/1580 patients (5%) did nonetheless receive routine follow-up imaging based on shared-decision making (the remaining 199/284 patients (70%) who received routine follow-up imaging participated in a clinical study with a study-specific follow-up including routine imaging). This results in a slight increase of the suspected overall survival in the control arm to 19.7 months (95% × 19.0 months + 5% × 32.0 months). The clinically relevant survival difference of 29.4 months vs. 19.7 months for the intervention and control arm, respectively, also approximates the mean survival difference of 9.5 months presented in the meta-analysis from Halle-Smith et al. [33]. These numbers correspond to a relative hazard (RH) of survival of 1.49, which is used to calculate the sample size of the study. Furthermore, as we expect a minimal level of loss to follow-up in this surveillance study, a censoring rate of 1% is expected each month.

To detect a 49% overall survival improvement (RH of survival 1.49) for patients in the intervention group, as compared with the control group, with a statistical power of 80% and a 0.05 two-sided significance level, a sample size of 306 patients is required. This calculation was based on the assumption of an exponential model, a median overall survival of 19.7 months in the control arm, a follow-up duration of 30 months, a drop-out rate of 1% and a baseline event rate of 3.5%. Following this calculation, we plan to include 306 patients in total: 153 patients in the recurrence-focused follow-up group and 153 patients in the non-standardized, symptomatic follow-up group.

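### The overall-survival comparison is an unadjusted log-rank test, valid but short of power if the baseline factors are prognostic; the prespecified adjusted Cox model could be made primary at little cost.

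*Protocol article*

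**What the plan says.** The primary endpoint, set under Outcomes {12}, is all-cause survival from surgery: "The primary outcome is overall survival, defined as the time from the date of PDAC resection until the date of either death from any cause".

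Statistical methods {20a} gives three analyses of it, by intention to treat:

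- The comparison of arms: "Log-rank test will be used to compare survival between the intervention and control group".
- A crude estimate: "Univariate Cox-proportional hazard analysis will be used to assess the crude effect of a recurrence-focused surveillance strategy on survival".
- An adjusted estimate: "In addition, adjusted effect estimates will be calculated using a multivariable Cox-proportional hazard model, including potential confounders for symptomatic PDAC recurrence".

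On the third, the text says "multivariable analysis is adjusted for 15 baseline covariates that are considered to be the most important". Ten factors are named. Five are continuous (age, performance status, CA 19-9, tumour size, positive nodes). Five are binary (sex, tumour location, margin, differentiation, adjuvant therapy). Under the article's rule that a categorical variable counts once per category, 5 + 5 × 2 = 15, so the list and the count agree.

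The factors are already to hand, as Plans for assessment and collection of outcomes {18a} notes: "Baseline characteristics of all trial participants are standardly collected as part of the PACAP and PACOPS projects". Multiple imputation of missing baseline values is planned under {20c}. No sentence labels one of the three analyses primary. The log-rank test is the only named test between arms.

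**The concern.** The adjusted model is given the wrong job. In a randomised comparison, confounding of the arm effect is removed in expectation, so control of confounding is a weak reason to adjust. The useful reason is power. In a survival model, leaving out strong prognostic factors pulls the arm hazard ratio towards 1 and weakens the test. The plan specifies and collects the factors, then leaves them out of the test that decides the primary question.

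The article itself calls the disease highly heterogeneous ({20b}) and describes these factors as the most important ones, so some prognostic value is a reasonable expectation. At stake is a missed true effect in a trial whose size is fixed and whose recruitment was nearly complete.

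**Working it through.** **1. The plan's own figure.** Inputs from Sample size {14}: "with a statistical power of 80% and a 0.05 two-sided significance level, a sample size of 306 patients is required"; relative hazard 1.49; exponential survival with control median 19.7 months; 30 months of follow-up; 1% censoring per month.

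- Deaths needed (Schoenfeld): (1.96 + 0.8416)² / (0.25 × (ln 1.49)²) = 7.849 / (0.25 × 0.1590) = 197.4.
- Control hazard: λ = ln 2 / 19.7 = 0.0352 per month.
- Probability of an observed death: λ/(λ + 0.01) × (1 − exp(−30(λ + 0.01))). In the control arm this is 0.578.
- If 1.49 multiplies the intervention hazard, the mean over arms is 0.644 and N = 197.4 / 0.644 = 306.4. This reproduces 306.
- If 1.49 lowers the intervention hazard, as hypothesised, the mean is 0.512. Then 306 patients give 306 × 0.512 = 157 deaths and 70.4% power.
- With the 28 months of accrual in Recruitment {15}, there are about 184 deaths and 77.1% power.

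The direction of the relative hazard is a separate matter. It is shown only because it sets the base power here.

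**2. Formula check of the gain.** If the covariates explain a share R² of the variation, information scales by 1/(1 − R²). Power is then Φ(|ln HR| × √(D / (4(1 − R²))) − 1.96). With D = 156.7 and R² = 0, this is Φ(2.496 − 1.96) = 70.4%.

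| R² | Gain from 70.4% (157 deaths) | Gain from 77.1% (184 deaths) |
|---|---|---|
| 0.05 | +2.2 | +2.1 |
| 0.10 | +4.5 | +4.2 |
| 0.20 | +9.3 | +8.5 |
| 0.30 | +14.3 | +12.7 |

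**3. Simulation.** Settings: 306 patients, 1:1; control median 19.7 months; 1% censoring per month; nine baseline covariates with equal weights; 3,000 trials per setting (6,000 at SD 0). The standard error of each power is about 0.8 points. The SD of the log-hazard score is an **assumption**, because the article gives no value. SDs of 0.3, 0.4, 0.6 and 0.8 correspond to R² of 0.05, 0.09, 0.18 and 0.28, from SD²/(SD² + π²/6). Row (a) holds the crude hazard ratio at 1/1.49. Row (b) holds the covariate-adjusted hazard ratio there. Cells show log-rank power → adjusted Cox power, in %.

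| SD | Effect held | Fixed 30 months | With 28 months' accrual |
|---|---|---|---|
| 0 | – | 70.5 → 69.4 (−1.1) | 77.3 → 76.0 (−1.3) |
| 0.3 | a | 72.2 → 74.3 (+2.1) | 76.3 → 78.5 (+2.2) |
| 0.3 | b | 67.8 → 70.2 (+2.4) | 73.7 → 75.3 (+1.5) |
| 0.4 | a | 69.6 → 73.1 (+3.5) | 77.1 → 82.0 (+4.8) |
| 0.4 | b | 65.7 → 70.1 (+4.3) | 71.7 → 76.8 (+5.1) |
| 0.6 | a | 69.9 → 78.9 (+9.0) | 74.0 → 84.9 (+10.9) |
| 0.6 | b | 59.2 → 68.6 (+9.4) | 62.9 → 74.8 (+11.9) |
| 0.8 | a | 67.5 → 81.4 (+13.9) | 73.7 → 87.6 (+13.9) |
| 0.8 | b | 52.9 → 68.6 (+15.7) | 55.5 → 73.7 (+18.1) |

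Repeat simulations with nine or ten covariates, some of them binary, gave the same pattern. Across all runs the change is about −2 to +3 points at SD 0 to 0.3, +4 to +7 at 0.4, +7 to +12 at 0.6 and +13 to +18 at 0.8. At SD 0.8 most settings fall between +13 and +16. The highest value occurs with accrual and the adjusted hazard ratio held at 1/1.49.

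**The case against.** The unadjusted log-rank test is a standard, valid test that holds its type I error, and it fits a sample size built on unadjusted medians. Choosing it is a preference about efficiency, not an error. The adjusted hazard ratio and its interval will be reported in any case. All of this stands, and it limits the point to an improvement.

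Two stronger readings are tempting, and the article supports neither.

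- A reader might take a loss of, say, 5 to 14 points as established. It is not: no prognostic strength is given. With weak covariates the gain is 3 points or less, and with uninformative ones adjusting costs 1 to 2. The simulations also assume correctly specified linear effects and no missing values, which favours the adjusted test.
- A reader might infer that, because one 0.05 threshold covers both analyses, either test may carry the claim, so type I error is inflated. The article states no such rule. It gives the log-rank test for comparing the arms and the Cox model for "In addition, adjusted effect estimates will be calculated using a multivariable Cox-proportional hazard model". The 0.05 sentence is a general threshold, not a decision rule.

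Timing also counts. At submission 219 of 306 patients were enrolled in a trial without blinding, and the monitoring board reviews main outcomes yearly. Changing the primary test at that stage costs credibility unless it is shown to be independent of the results.

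**Conclusion.** The point holds as a low-cost improvement. The test that compares the arms leaves out prespecified factors already being collected, and the reason given for the adjusted model is confounding, which randomisation largely deals with.

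The size depends on an assumption the article cannot settle. It runs from a loss of up to about 2 points if the factors are uninformative to a gain of 13 to 18 points at a score SD of 0.8. The unadjusted base is about 51 to 72% with a fixed 30 months, or 55 to 77% with accrual. The lower ends arise only when the covariate-adjusted hazard ratio, not the crude one, equals 1/1.49. That the log-rank test is primary is inferred from its being the only named test between arms.

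**What to change.** In {20a}, before any outcome data by arm are examined, state that the primary test and estimate for overall survival is the arm effect in the intention-to-treat Cox model adjusted for the listed covariates fixed before randomisation. That leaves nine of the ten. Adjuvant therapy is omitted because randomisation takes place within 3 to 4 months of surgery and such therapy may start afterwards. Use the multiple imputation already planned in {20c}. Give precision, not confounding, as the reason for adjusting. Keep the Kaplan-Meier curves, log-rank test and crude hazard ratio as supportive.

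Only wording changes; no new data or patients are needed. The costs are:

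- The primary hazard ratio becomes conditional on the covariates, and the text should say so.
- The result relies on imputed baseline values.
- Up to about 2 points of power are lost if the factors are not prognostic.
- The change comes late in an open-label trial, so a dated amendment should record that it was made without sight of outcomes.
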